# Investigation into repetitive concussion in sport (RECOS): study protocol of a prospective, exploratory, observational cohort study

**DOI:** 10.1136/bmjopen-2019-029883

**Published:** 2019-07-04

**Keywords:** concussion, traumatic brain injury, sport concussion, biomarkers, imaging, postconcussion syndrome

## Abstract

**Introduction:**

Sport-related concussion management remains a diagnostic dilemma to clinicians in all strata of care, coaching staff and players alike. The lack of objective diagnostic and prognostic biomarkers and over-reliance on subjective clinical assessments carries a significant health risk of undiagnosed concussive episodes and early return to play before full recovery increasing the risk of sustaining additional concussion, and leading to long-term sequelae and/or unfavourable outcome.

**Objective:**

To identify a set of parameters (neuroimaging with neurophysiological, biological and neuropsychological tests) that may support pitch-side and outpatient clinical decision-making in order to objectively diagnose concussion, determine the severity of injury, guide a safe return to play and identify the potential predictors of the long-term sequelae of concussion.

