**Methods and analysis:**

An exploratory, observational, prospective, cohort study recruiting between 2017 and 2020. The participants will have a baseline preseason screening (brain imaging, neuropsychological assessments, serum, urine and saliva sampling). If a screened player later suffers a concussion and/or multiple concussions then he/she will be assessed again with the same protocol within 72 hours, and their baseline data will be used as internal control as well as normative data. Inferential statistical analysis will be performed to determine correlations between biological, imaging techniques and neuropsychological assessments.

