## Introduction

Sport-related concussion (SRC) is defined as a brief period of loss of consciousness, memory loss, feeling dazed or confused following trauma to the head, face or neck, and is a common cause of mild traumatic brain injury (mTBI).^1 2^ In the USA, the Centers for Disease Control and Prevention estimate that 1.6–3.8 million concussions occur in sports and recreational activities annually, but there is fear that the number may be much larger, as the majority of incidents are unrecognised or unreported.^3^

The majority of patients improve rapidly following a single concussion, but 10%–20% of individuals have persistent symptoms (eg, headache, dizziness, fogginess, imbalance and anxiety) at 3 months. In a minority (2%–4%) the symptoms may become permanent.^4 5^ There is a higher risk of sustaining further concussion if they returned to play before full recovery which prolongs recovery time after each incident.^4 5^

Certain groups of patients, such as athletes, soldiers and children are at greater risk of repetitive mTBI; potentially leading to a catastrophic form of brain injury known as second impact syndrome (SIS), thought to be due to the second insult occurring during a window of metabolic vulnerability of the brain.^6–8^

In susceptible individuals, repetitive head trauma has been linked to early neurodegenerative conditions such as Parkinson’s, amyotrophic lateral sclerosis and Alzheimer’s disease. The risk of neurodegenerative conditions has been demonstrated to treble in retired professional American football players^9^ and following the media attention dedicated to this issue, the link between mTBI and chronic traumatic encephalopathy (CTE) has become a major public concern.^10 11^ Compounding this problem is the fact that athletes, like soldiers, are highly trained, young, fit, motivated individuals proven to under-report concussive symptoms.^12 13^

Athletes are, therefore, at risk of SIS and CTE. Currently, there is no validated clinical biomarker available to assess mTBI, SIS and cumulative brain damage, leading to an over-reliance on self-reporting of symptoms in the management of mTBI.^14^

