**Figure 1 F1:**
[figure not shown]
Flowchart of study procedures. ^*^Urine pregnancy test will be performed first for all female participants.

MRI scanning (~1 hour) will be performed using a 3T MRI scanner at the QEHB. First of all, a standard structural MRI scan will be acquired (T1-weighted, T2-weighted and T2*-weighted and FLAIR images), followed by MR spectroscopy (1H-MRS) (NAA/choline, NAA/creatine and choline/creatine ratios),^29^ resting-state functional MRI (fMRI) (subjects are awake, eyes closed, motionless), diffusion tensor imaging (DTI) and magnetic resonance elastography (MRE) on brain will be performed to obtain quantitative values for tissue mechanical parameters.^30 31^

Prior to any female participant undergoing MRI, a pregnancy test will be performed after the expressed consent of the individual.

These assessments will be repeated in the QEHB or sports facilities during the follow-up and when the individual is deemed fit to return to play, until normalisation of the 1H-MRS or self-reported symptoms are observed.

The near-infrared spectroscopy (NIRS) is a safe non-invasive brain imaging technique that utilises near-infrared (NIR) light absorption to assess brain oxygen saturation. The NIR light is currently widely used in clinical practice (eg, pulse oximeter and brain monitoring during cardiac surgery). fNIRS measurements are performed once within 48–72 hours from the injury using a frequency domain NIRS device (ISS IMAGENT; Champaign, Illinois, USA) and a digitizer (POLHEMUS FASTRAK; Colchester, Vermont, USA).^32 33^

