### Outcome measures and statistical analysis

The recruitment target is based on the size of the convenient sample that can be recruited (~400); power calculation do not apply as the investigation is explorative at this stage. The sample size will be open-ended and reviewed after 3 years.

Correlations between biomarkers, 1H-MRS, fMRI, MRE, DTI, fNIRS, neuropsychological scores, motor and coordination parameters will be assessed and reported with standard parametric statistical tests after normalisation of data or non-parametric test if normalisation were not possible. Time to resolution of symptoms will be compared for all the above modalities, as well as self-reported outcomes. Biochemical and imaging data will also be analysed with standard group comparison statistics (eg, t-test on normalised data or Mann-Whitney on non-normalisable data).

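### The aim of finding predictors of long-term sequelae has no matching late outcome in the article's text, and follow-up can be read as ending on 1H-MRS, itself a candidate marker

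*Protocol article*

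**What the plan says.** **Aim.** The abstract's Objective lists four purposes: diagnosis, severity, safe return to play, and to "identify the potential predictors of the long-term sequelae of concussion".

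**Schedule.** After a concussion, according to the abstract (Methods and analysis), "he/she will be assessed again with the same protocol within 72 hours". One modality is not repeated at all: "fNIRS measurements are performed once within 48–72 hours from the injury". For the rest, Study design (text after the Figure 1 legend) says that assessments recur "during the follow-up and when the individual is deemed fit to return to play", and sets the end point of that repetition as "until normalisation of the 1H-MRS or self-reported symptoms are observed". The text gives no calendar visit, no minimum duration and no contact after recovery.

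**Outcomes.** Under Outcome measures and statistical analysis, the only time-based outcome is this: "Time to resolution of symptoms will be compared for all the above modalities, as well as self-reported outcomes". The other analyses are correlations between modalities and two-group comparisons. No late outcome is named, and long-term sequelae are not defined.

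**Background.** The Introduction describes late consequences at three levels: symptoms at 3 months in 10%–20%, then "In a minority (2%–4%) the symptoms may become permanent", and finally neurodegenerative disease.

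**The concern.** A prognostic aim needs an outcome that is later than the predictors and is looked for in the same way in everyone. Here the stated schedule is driven by recovery, and one of the two recovery criteria is 1H-MRS. The outcome section also lists 1H-MRS among the measures to be correlated with the others, so it is a candidate predictor.

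If normalised 1H-MRS can end an athlete's follow-up, the length of observation depends on that marker. Persistent symptoms would then be recorded less often in athletes whose 1H-MRS recovers early, whether or not those athletes have fewer of them. An association between abnormal 1H-MRS and persistent symptoms could come from this rule alone. Markers that move with 1H-MRS would carry the same distortion. This would be bias, and a larger sample would not remove it.

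Apart from this, symptoms that return or first appear after normalisation would not be recorded under any schedule given in the text.

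**Working it through.** The main check compares the stated aim, follow-up rule and outcomes. The plan has no power calculation to reproduce: about 400 is given as a convenience sample.

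**Step 1: the two readings of the follow-up rule.** The sentence joins 1H-MRS and self-reported symptoms with *or*.

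- *Reading A: either criterion ends follow-up.* Take an athlete with normal 1H-MRS and continuing symptoms. One criterion is met, so repetition can stop. This athlete is a potential case of persistent symptoms, and the case may go unrecorded.
- *Reading B: follow-up continues until symptoms resolve.* The same athlete stays under observation, and the duration of symptoms is recorded. An athlete who recovers has no further stated contact, so relapse or later sequelae are not captured.

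Reading A makes ascertainment depend on a candidate predictor. Reading B supports an analysis of symptom duration and nothing later.

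**Step 2: aim against outcomes.** The aim concerns long-term sequelae. The listed outcomes stop at resolution of symptoms. Under either reading, no outcome is observed at one common late time in all concussed athletes.

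**Step 3: how many late cases might there be? (illustration only)** Inputs: n = 400, the figure in Study design and in the outcome section; rates of 10%–20% at 3 months and 2%–4% permanent, from the Introduction. Assumed for the illustration and not in the plan: full recruitment, no loss to follow-up, two-sided alpha 0.05, 80% power, no adjustment for multiple markers, and a reference difference of 0.5 SD.

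- Cases: e = 400 × rate.
- Detectable difference between cases and non-cases, in SD: d = (1.960 + 0.842) × √(1/e + 1/(400 − e)).
- Power at 0.5 SD: Φ(0.5 / √(1/e + 1/(400 − e)) − 1.960).

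| Outcome | Rate | Cases / non-cases | Detectable d (SD) | Power at 0.5 SD |
|---|---|---|---|---|
| Permanent symptoms | 2% | 8 / 392 | 1.001 | 29% |
| Permanent symptoms | 4% | 16 / 384 | 0.715 | 50% |
| Symptoms at 3 months | 10% | 40 / 360 | 0.467 | 85% |
| Symptoms at 3 months | 20% | 80 / 320 | 0.350 | 98% |

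Worked row: for 10%, √(1/40 + 1/360) = 0.1667; 2.802 × 0.1667 = 0.467; 0.5/0.1667 − 1.960 = 1.04, and Φ(1.04) = 0.85.

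These figures do not measure the ascertainment bias. They show only which late outcome could be explored if it were observed in everyone.

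**The case against.** The best defence has four parts.

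1. *The wording is ambiguous.* If athletes are followed until symptoms resolve, those with persistent symptoms are the ones who remain under observation, and prolonged symptoms can be identified from the resolution times. This stands. A reader might infer that follow-up ends at the first normalisation of either measure, or that recovered athletes are never seen again. The article says neither; it leaves the point open and states no later contact.
2. *Figure 1 and the full protocol may hold a schedule.* Figure 1 is not available here, and an article often leaves visit calendars to the full protocol. This also stands, so the lack of a fixed date is weak evidence by itself. A calendar would not settle the *or*, however, which is a stated rule and not an omitted detail.
3. *The study is exploratory and speaks of potential predictors.* This justifies the lack of a power calculation. It does not remove the need to observe the outcome in a way that does not depend on the predictors.
4. *The case counts are borrowed.* The Introduction gives the rates after referring to a single concussion, while the cohort mixes singly and multiply concussed athletes and excludes those admitted to hospital or with abnormal initial scans. The number 400 is an upper figure in Study design, and the outcome section calls the sample size open-ended. All of this stands, so the counts serve only as illustration. It is also tempting to judge them by events per variable in a multivariable model, but the article plans correlations and group comparisons and states no such model.

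**Conclusion.** The point holds in a limited form. As the text stands, the follow-up rule and the listed outcomes support analysis of how long symptoms last. They do not support identifying predictors of long-term sequelae beyond that. Under the literal reading they also let 1H-MRS, a candidate marker, decide how long symptoms are observed.

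A reader might go further and conclude that the objective cannot be met. The documents do not support that: on the other reading of the rule, prolonged symptoms are observed, and a late schedule may exist in Figure 1.

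The size of any bias cannot be derived from the documents. On the assumptions given in the working, 3-month symptoms (40 to 80 cases) would be a workable exploratory outcome. Permanent symptoms (8 to 16 cases) would be too few for more than description. One of four stated aims is affected and the remedy is small, so this should be changed, but it does not undermine the study as a whole.

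**What to change.** First, reword the follow-up sentence in Study design so that research follow-up of symptoms does not end on 1H-MRS normalisation alone, and reconcile it with any schedule in Figure 1. This concerns when research data are collected and leaves return-to-play decisions untouched.

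Then do one of the following:

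- **(a) Keep the aim.** Add one short remote symptom checklist at a common time after injury for every concussed athlete, regardless of earlier normalisation. Three months is one candidate, because the Introduction already uses it. Name persistent symptoms at that time as the prognostic outcome, and say whether the investigators regard it as long-term.
- **(b) Narrow the aim.** Replace predictors of long-term sequelae with predictors of time to symptom resolution.

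In both cases, state that permanent sequelae will be described only.

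**Cost.** Option (a) needs one brief questionnaire per athlete and an amendment. Recruitment was planned from 2017 and the article appeared in 2019, so athletes already past the chosen time may be missed; their number should be reported. Option (b) changes only wording, at the price of a narrower claim.

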**Methods and analysis:**

An exploratory, observational, prospective, cohort study recruiting between 2017 and 2020. The participants will have a baseline preseason screening (brain imaging, neuropsychological assessments, serum, urine and saliva sampling). If a screened player later suffers a concussion and/or multiple concussions then he/she will be assessed again with the same protocol within 72 hours, and their baseline data will be used as internal control as well as normative data. Inferential statistical analysis will be performed to determine correlations between biological, imaging techniques and neuropsychological assessments.

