At present, the mainstream assessment of mTBI both in sports and in the primary/secondary healthcare setting involves the functional and symptomatic assessment of an individual using neurocognitive tests.^15^ These tests have significant limitations, particularly the lack of baseline/premorbid measurement in terms of sensitivity and specificity^16 17^ and the susceptibility to multiple confounding factors^18^ such as musculoskeletal injury and/or premorbid disability. This together with their requirement for a high level of engagement and concentration limits their application in outpatient clinic or pitch-side.

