## Methods and analysis

### Study design

A cohort of contact sport athletes (eg, rugby, football, American football and so on) will be recruited throughout the West Midlands region and through referrals from sports clubs anywhere in the Great Britain.

The assessments are carried out in two settings: (1) the sports clubs with clinical areas dedicated to sample taking and data collection and (2) Birmingham concussion clinic at the Queen Elizabeth Hospital Birmingham (QEHB) or at the University of Birmingham (UoB).

Eligible individuals will be identified by key members of their coaching staff who have been trained regarding the inclusion specifications and the procedures involved in recruitment (table 1). Athletes who sustain a head injury during competition or training will be advised to attend an assessment session between 48 and 72 hours after their concussion at the concussion clinic at QEHB, although attending directly or as soon as is practically possible will be advised. Should the injury be sufficiently serious that the attending staff believes immediate medical assistance or transfer to the nearest emergency department is required, then standard clinical procedures should be followed in these cases.

**Table 1 T1:** Summary of eligibility criteria

Inclusion criteria	Exclusion criteria
Male or female athletes participating in contact sports, aged 16–65 years, with fluent English speaking.	Individuals who require hospital admission after initial assessment for their TBI.
Single or repetitive mTBI sustained in contact sport <72 hours prior to assessment.	Intracranial haemorrhage, brain tissue injury or non-TBI related pathologies on initial CT/MRI scan.
Normal neurological objective examination at the time of enrolment.	Pregnancy (urine pregnancy test will be performed for confirmation).
	Any history of neurodegenerative pathology or any recent or ongoing illness affecting the central nervous system (eg, Parkinson’s, multiple sclerosis, meningitis, epilepsy, neoplasm).
	History of chronic alcoholism or drug abuse.
	Any other sustained injury that requires hospital admission.

mTBI, mild traumatic brain injury.

Consent to participate in the study will be obtained from the participants in a standardised written consent form. Details of the consent will be maintained as per the UoB and University Hospitals Birmingham NHS Foundation Trust guidelines, and maintained for the study period and archived thereafter.

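### The stated analyses do not estimate how well a marker classifies concussed athletes, and the preseason controls leave concussion mixed with recent play

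*Protocol article*

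**What the plan says.** **Aim.** The abstract's Objective seeks a set of parameters "that may support pitch-side and outpatient clinical decision-making in order to objectively diagnose concussion, determine the severity of injury, guide a safe return to play". It names predictors of long-term sequelae as a further purpose. The strengths and limitations list repeats the diagnostic purpose. The design is described as "An exploratory, observational, prospective, cohort study recruiting between 2017 and 2020".

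**Analysis.** The abstract names one inferential analysis: "Inferential statistical analysis will be performed to determine correlations between biological, imaging techniques and neuropsychological assessments". The section Outcome measures and statistical analysis names three:
- correlations: "Correlations between biomarkers, 1H-MRS, fMRI, MRE, DTI, fNIRS, neuropsychological scores, motor and coordination parameters will be assessed and reported";
- a comparison of time to symptom resolution across modalities and self-reported outcomes;
- group comparisons: "Biochemical and imaging data will also be analysed with standard group comparison statistics (eg, t-test on normalised data or Mann-Whitney on non-normalisable data".

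The groups to be compared are not named there. No reference standard, threshold, sensitivity, specificity or AUC is mentioned.

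**Controls.** The abstract and Study design give two: the athlete's own preseason baseline, and an uninjured cohort that supplies normative data at preseason screening. MRI may not be done in all of them.

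**Cases.** On the post-injury side: "Athletes who sustain a head injury during competition or training will be advised to attend an assessment session". The visit is advised at 48 to 72 hours or sooner. Table 1 excludes other injuries only when they require hospital admission. Study design also provides for repeat assessments during follow-up and at return to play.

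**The concern.** Two gaps lie between the aim and what is described.

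First, a correlation between two modalities shows that they move together. A significant group difference shows that two averages or distributions differ. Neither tells a clinician how often a marker would be right about the athlete in front of them, which is what a diagnostic aim needs. With up to 400 concussed athletes, very small shifts reach significance, so a long list of significant markers could be reported without any indication of which are useful.

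Second, cases are measured after contact play and the non-concussed controls before the season. The contrast therefore carries recent contact, exertion, minor bodily injury and time in season along with concussion. Own-baseline control removes stable differences between people but none of these. The Introduction itself faults existing neurocognitive tests for confounders "such as musculoskeletal injury and/or premorbid disability". What is at stake is that markers of play could be carried forward as candidate markers of concussion.

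**Working it through.** **The plan's own figure.** There is none to reproduce. The target of about 400 is a convenience sample, and the article says that a power calculation does not apply. The number of controls, the effect sizes and alpha are not given. The figures below are illustrations under stated assumptions: one normally distributed marker, equal SD of 1, independent groups, two-sided alpha 0.05.

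**Formulas**, with d the shift in SD units:
- power = Φ(d / √(1/n₁ + 1/n₂) − 1.96)
- AUC = Φ(d / √2)
- sensitivity at 90% specificity = Φ(d − 1.2816)

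**Step 1: significance against classification.** For d = 0.5 and an assumed 100 per group:
- power = Φ(0.5 × √50 − 1.96) = Φ(1.576) = 0.94
- AUC = Φ(0.354) = 0.64
- sensitivity = Φ(−0.782) = 0.22

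For d = 0.8, AUC = Φ(0.566) = 0.71 and sensitivity = Φ(−0.482) = 0.32.

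With 400 concussed athletes, the shift detectable at 80% power is d = (1.96 + 0.8416) × √(1/400 + 1/n₂):

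| Assumed controls | Detectable d | AUC | Sensitivity at 90% specificity |
|---|---|---|---|
| 100 | 0.313 | 0.588 | 17% |
| 200 | 0.243 | 0.568 | 15% |
| 400 | 0.198 | 0.556 | 14% |

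For correlations at n = 400, the smallest significant r is tanh(1.96/√397) = 0.098.

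**Step 2: play without a concussion effect.** Assume that concussion does nothing to a marker and that recent play shifts it by m SD. The power formula with d = m gives the probability of a significant difference from preseason:

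| Assumed m | 400 v 400 | 400 v 100 | AUC v preseason |
|---|---|---|---|
| 0.2 | 0.81 | 0.43 | 0.56 |
| 0.3 | 0.99 | 0.77 | 0.58 |
| 0.5 | about 1.00 | 0.99 | 0.64 |

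Against equally play-exposed, non-concussed athletes, the AUC would be 0.50 in every row. The documents give no value for m; these are assumptions.

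**Step 3: could the planned sample support an accuracy analysis?** Using the Hanley-McNeil standard error with 400 cases and an assumed 100 to 400 independent controls, the 95% CI half-width is 0.052 to 0.036 at AUC 0.70, 0.041 to 0.031 at AUC 0.80, and 0.027 to 0.022 at AUC 0.90. It could.

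**The case against.** The study is openly exploratory. Its objective is to identify parameters that may support decisions, and diagnosis is one of several purposes. Correlations and group comparisons are legitimate tools for finding candidates. The article is a condensed account, its tests are given as examples, and an accuracy analysis could sit in a plan that is not shown. All of this stands, and it limits the point to a mismatch between stated aim and stated analyses. It does not answer the comparator problem, because no later plan can analyse controls who were never sampled. Candidate finding also needs a contrast that can be ascribed to concussion.

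A reader might infer more than the text supports:
- *That the analyses cannot show diagnostic value at all.* Too strong: the Mann-Whitney U divided by n₁n₂ is the empirical AUC, so the named test already contains the quantity. It is simply not planned for or reported as such.
- *That preseason data are the only contrast.* The follow-up and return-to-play assessments give a later within-person comparison. It does not replace play-exposed controls, but it helps.
- *That cases are measured straight after a match against resting controls.* The advised visit is at 48 to 72 hours, though sooner is allowed. Injury may occur in training, and the controls are described as preseason, not resting. How much exertion effect persists is not stated.
- *That head-injured athletes judged not concussed are turned away.* No such group is described; the sentence that invites head-injured athletes times the visit from their concussion.
- *That bodily injury and exertion are ignored.* Injuries needing admission are excluded, and prior physical activity is recorded by questionnaire. Neither separates play from concussion when no control is play-exposed.

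**Conclusion.** The point holds in a limited form. The article states a diagnostic aim, but none of its three named analyses is set up to estimate classification. All non-concussed controls described are preseason, so a difference from them is not cleanly attributable to concussion.

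The size is illustrative. Under the single-marker normal model, a 0.5 SD shift gives 94% power at 100 per group with AUC 0.64 and 22% sensitivity at 90% specificity. A play-only shift of 0.3 SD would be significant with probability 0.77 to 0.99, depending on the number of controls. Shifts, control numbers and independence are assumptions. Paired analyses would change the power, and a panel could classify better than one marker.

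This should be changed because it affects what the study may claim. It does not make the study unable to find candidate markers.

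**What to change.** In Outcome measures and statistical analysis, for the diagnostic aim:
1. Add the AUC and the sensitivity at a fixed specificity, each with a 95% CI, comparing post-concussion with baseline and normative values. Take clinical diagnosis as the reference standard. Respect pairing by athlete and clustering of repeat concussions.
2. Use cross-validated or penalised estimates for marker panels. Keep correlations as supporting analyses.
3. Use the follow-up and return-to-play assessments as a second within-person contrast. Repeats run until 1H-MRS or symptoms normalise, so for those two measures the last value is not an independent check.
4. Record concurrent bodily injury and time since exertion in the concussed athletes, and report whether marker levels vary with them.
5. State that accuracy against preseason values may be inflated by play exposure and does not establish specificity for concussion.

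Accuracy of the change from own baseline cannot be estimated as the study stands, because non-concussed athletes are not described as having a second measurement.

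The cost of items 1 to 5 is a little more analysis, two recorded items and more cautious conclusions. The stronger remedy is a play-exposed, non-concussed comparison group, for example on fluid and cognitive measures only. It is optional: it needs extra visits and assays, and on the full battery it would add about an hour of MRI per athlete, where resources are already limited.
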